## Abstract

**Background:**

One of the most important causes of maternal mortality and severe morbidity worldwide is post partum haemorrhage (PPH). Factors as substandard care are frequently reported in the international literature and there are similar reports in the Netherlands. The incidence of PPH in the Dutch population is 5% containing 10.000 women a year. The introduction of an evidence-based guideline on PPH by the Dutch society of Obstetrics and Gynaecology (NVOG) and the initiation of the MOET course (Managing Obstetrics Emergencies and Trauma) did not lead to a reduction of PPH. This implies the possibility of an incomplete implementation of both the NVOG guideline and MOET-instructions. Therefore, the aim of this study is to develop and test a tailored strategy to implement both the NVOG guideline and MOET-instructions

**Methods/Design:**

One step in the development procedure is to evaluate the implementation of the guideline and MOET-instructions in the current care. Therefore measurement of the actual care will be performed in a representative sample of 20 hospitals. This will be done by prospective observation of the third stage of labour of 320 women with a high risk of PPH using quality indicators extracted from the NVOG guideline and MOET instructions. In the next step barriers and facilitators for guideline adherence will be analyzed by performance of semi structured interviews with 30 professionals and 10 patients, followed by a questionnaire study among all Dutch gynaecologists and midwives to quantify the barriers mentioned. Based on the outcomes, a tailored strategy to implement the NVOG guideline and MOET-instructions will be developed and tested in a feasibility study in 4 hospitals, including effect-, process- and cost evaluation.

**Discussion:**

This study will provide insight into current Dutch practice, in particular to what extent the PPH guidelines of the NVOG and the MOET-instructions have been implemented in the actual care, and into the barriers and facilitators regarding guideline adherence. The knowledge of the feasibility study regarding the effects and costs of the tailored strategy and the experiences of the users can be used in countries with a relatively high incidence of PPH.

**Trial Registration:**

ClinicTrials.gov NCT00928863

## Background

The major cause of maternal death worldwide is post partum haemorrhage (PPH, blood loss of >1000 cc during and after delivery), with about 146.000 deaths annually [1]. Although this is largely due to deaths in developing countries, even in the Netherlands it is still in the top four of maternal deaths [2]. In this country the reported incidence of PPH is 5% in the secondary care, affecting about 10.000 women annually [3]. In the Lemmon trial (2004-2006), in which a large part of Dutch hospitals participated, all severe maternal morbidity was documented and PPH in absolute number is the major factor contributing to severe maternal morbidity [4]. Causes such as substandard care are frequently reported in the international literature. In a study in France, suboptimal care factors were found in 38% of women with PPH > 1500 cc and in 70% of women who died of PPH. In audits, performed in PPH cases of the Lemmon trial, suboptimal care factors were also common in the Dutch population (unpublished data). A logical assumption is that these factors can be overcome by the use of evidence based guidelines. The Dutch Society of Obstetrics and Gynaecology (NVOG) developed and disseminated an evidence-based guideline about PPH, in which the best scientific evidence is summarized [5]. Furthermore, in 2003 the MOET course (Managing Obstetric Emergencies and Trauma), an ATLS-based course of the RCOG, translated to the Dutch situation, was introduced, in which stepwise and practical instructions to prevent PPH were given [6]. However, without tailor-made implementation, in general large gaps exist between best evidence as described in guidelines and daily practice [7,8]. This also applies to PPH. Both the dissemination of the evidence-based guideline about PPH and the MOET course did not lead to a reduction in PPH: nationwide the incidence of PPH was 3.8% in 2003 and 5.2% in 2006 [3]. An incomplete implementation of both the NVOG-guideline and the MOET-instructions is expected.

## Methods/Design

### Objectives

The first objective of this study is to asses to what extent the NVOG guidelines and the MOET-instructions have been implemented in current care in the Dutch practice. The second objective is to study barriers and facilitators for guideline adherence. Finally based on these findings a tailored implementation strategy will be developed and tested on effects, experiences and costs.

### Design and study population described per step

### Objective 1

To assess the actual care of Dutch gynaecologists and midwives for patients at high risk for PPH (actual care study).

### Design

#### Developing quality indicators

Before actual care can be measured, quality indicators have to be developed regarding the process, structure and outcome of care. These indicators have to be based on the key recommendations from the NVOG guideline on PPH and the MOET-instructions. The indicator development will be performed according to the RAND-modified Delphi method [9]. First the key recommendations from the NVOG guideline on PPH and the MOET-instructions will be extracted and relevant indicators from international literature will be added. Subsequently, the relevance of all these key recommendations will be tested in two rounds among an independent panel about 15 experts consisting of guideline writers, Dutch MOET board members and instructors, NVOG-members of the subcommittee Implementation and Quality, gynaecologists, haematologist and anaesthesiologist. In the first round the gathered recommendations will be edited in a written questionnaires for the expert panel where the experts are asked to score the key-recommendations on a 9-point Likert scale ranging from 1 = not relevant to 9 = extremely relevant, with respect to their impact on both 'health gain' and 'overall efficacy. In addition, a top-5 ranking of recommendations is asked in which they consider 'most important' and 'representative' to assess the quality of clinical performance. In this round the experts have the possibility to provide comments and add additional items as well. Of the returned questionnaires, the median scores on 'health gain' and 'overall efficacy' are calculated per recommendation and are rated valid if they match the criteria described by Campbell [10]. Secondly, based on the top-5 ranking of recommendations, a list with scores reflecting the weight that experts assigned to each recommendation will be created. In a second round, in a consensus meeting with all the experts these listings will be used as feedback. During this meeting this feedback will be discussed and the former rankings will be reconsidered with the aim to reach consensus about the most important recommendations to assess the quality of clinical performance regarding the adherence to the NVOG guideline on PPH and the MOET-instructions. The selected key recommendations will be operationalized in measurable elements.

#### The practical measurement of actual care

In an observational multi-centre study, actual care will be measured by video monitoring the third stage of delivery and a medical record search among 320 high risk patients for PPH in 20 hospitals. In all participating clinics, all delivery rooms will be set up with a digital camera. In order to avoid anxiety, bias or refusal of participation among the care-givers, it is made clear that none of the direct colleagues or patients will be able to see the images and that these images cannot be claimed by the patient in case of an adverse outcome. The images will be analyzed by the researcher and in a random selected subset by one of the project leaders to assess the extent of adherence to the developed quality indicators. Additional information for indicator adherence will be searched in the medical records of the videotaped patients. In this manner, deviations from the indicators can be outlined. This study will provide us with reliable information about current practice in the Netherlands.

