### Design

Based on the results of step 1 and 2, a tailored implementation strategy will be developed to increase the adherence to the recommendations. Because different barriers at different levels are expected, it is very likely that a strategy with different implementation elements directed at both professional and organizational level will be developed. At this moment, we have some hypotheses about expecting limitations in actual care. At the level of the guideline/MOET-instructions itself we think that the guideline can be more specific; the description of the desired care is not detailed enough. The desired care can be described in a detailed and structural manor by the development of "bundles". These bundles are defined as a group of interventions related to a disease process that, when executed together, results in better outcome than when implemented individually. A second limitation could be a delayed time interval between events and taken actions, (right actions taken too slowly due to individual decisions or organizational factors). The solution could also be describing the desired care in bundles in the guideline and on organizational level an improvement process can be undertaken if the exact problem can be identified for example; multidisciplinary clear agreements. At the level of the professionals, a lack of knowledge/insight in own performance can be an impending factor. The installed monitors could be used to constant audit and feedback their performance, both individual and in review conferences and team training could be an intervention. However, due to uncertainty of existing barriers and facilitators the strategy can not be worked out in detail now.

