### Intervention

The tailored improvement strategy will be implemented and evaluated in a feasibility study in nine months. The study will be performed in 4 hospitals (also participating in the actual care study) and consists of three evaluations:

a) To obtain an indication of the effect of the implementation strategy, the adherence to the developed indicators will be measured before (= actual care study) and after the introduction of the newly developed strategy, using videotaping and a medical record search (see step 1b). For the after-measurement we will include about 100 patients.

b) A process evaluation will be performed to study the experiences of the clinicians and patients with the changed care and also to study the extent by which clinicians and eventually patients use the elements of the strategies and their experiences (e.g. satisfaction and feasibility) with these elements. To achieve this, process information will be gathered in a qualitative study in the 4 participating hospitals and individual interviews will take place among the different involved gynaecologists, midwives and patients.

c) A cost analysis of the tested implementation strategy will take place. The perspective of this analysis will be the health care perspective. The costs of the implementation strategy will be estimated by an Activity Based Costing approach focusing on activities performed to implement the NVOG-guideline on PPH and the MOET-instructions, with the costs accumulated at the activity level(s) of the health care implementation processes. The costs of implementation of the guidelines and consolidation consist of personnel and material costs. The input of resources will be assessed by collecting volumes of consumed resources and multiplying these by the price of each resource unit. The prices of each resource unit will be based on standard costs, market prices or self-determined costs [11]. In the analysis, the implementation costs will be related to the difference in percentage of patients treated according to the guideline indicators in the situation before and after the implementation of the NVOG-guideline on PPH and the MOET-instructions

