#### Feasibility study

To get an indication of the effectiveness of the strategy the primary outcome measure is the adherence to developed quality indicators. Other outcome measures are the experiences of the participants (both professionals and patients) with the elements of the strategy and with the changed care. Also the cost of the tested strategy will be measured.

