#### Analysis of the feasibility study

In the effectuation the proportion of patients that are treated in accordance with the guidelines (analysed on the basis of the indicator set) before and after implementation of the guidelines will be established. Both univariate and multivariate (multi-level) analyses are performed to demonstrate the effect of the implementation strategy in increasing the proportion of patients who are treated according to the guidelines. In addition, for the process evaluation, frequencies are used to asses the experiences of the professionals and patients to the implementation programme elements. Analyses of the costs of the implementation strategy will be conducted by multiplying the volumes of consumed resources with the price of each resource unit.

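### The before recordings must be scored before the after recordings exist, and no masked or mixed-order re-read is described, so a shift in video scoring cannot be separated from the before-after change in adherence

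*Protocol article*

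**What the plan says.** Objective 1, under The practical measurement of actual care, names the readers: "The images will be analyzed by the researcher and in a random selected subset by one of the project leaders". Video is not the only source: "Additional information for indicator adherence will be searched in the medical records of the videotaped patients".

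Objective 3, Intervention, evaluation a) carries this method into the feasibility study, where adherence "will be measured before (= actual care study) and after the introduction of the newly developed strategy, using videotaping and a medical record search", with a reference back to the step 1 procedure. On the size of the second sample: "For the after-measurement we will include about 100 patients".

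The order of events follows from Objective 3, Design: "Based on the results of step 1 and 2, a tailored implementation strategy will be developed to increase the adherence to the recommendations".

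Under Outcome measures, Feasibility study: "To get an indication of the effectiveness of the strategy the primary outcome measure is the adherence to developed quality indicators". Under Analysis of the feasibility study: "Both univariate and multivariate (multi-level) analyses are performed to demonstrate the effect of the implementation strategy". Evaluation c) of the Intervention section relates the implementation costs to the same before-after difference.

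The article does not mention masking readers to period, reading the two sets of recordings together, or re-reading the baseline video. It also does not say what share of recordings is read twice or whether that subset covers both periods.

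**The concern.** Scoring care from video usually calls for some judgement. A reader may become stricter or more lenient over months, or may expect better care once a strategy is in place. In most designs such a shift is spread over the groups compared. Here reading time and period coincide: baseline scores are needed to build the strategy, and the after recordings are made only once it has been introduced. There is no concurrent group scored at the same times that would show the drift.

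The before-after change in adherence is the primary result of the feasibility study. It is also the denominator of the cost comparison, so a false gain would make the strategy look cheaper per point of improvement. The Discussion then makes an indication of effectiveness one of three conditions for a randomised study, alongside feasibility and low cost.

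Recordings, unlike bedside observations, can be read again. The plan has the means to remove much of this problem and describes no use of them.

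**Working it through.** **1. Does the design fix the reading order?** The article states no reading order, but two of its statements force one. The strategy is built on the results of step 1, so baseline adherence must have been scored before the strategy exists. The after recordings are made following its introduction, so they are scored later. The before measurement is identified with the actual care study, so unless a re-read is added, the comparator is the early set of scores.

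**2. Can the analysis separate a scoring shift?** Write observed adherence as true adherence plus a reader shift *s* that applies to the later reading. The observed difference is then (true after − true before) + *s*. Every before score has the early reading time and every after score the late one. Period and reading time are therefore the same variable in the model. Hospital or clinician random effects change the standard error but cannot estimate *s* apart from the period effect.

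**3. The article's own figures** (Sample size calculation actual care study). These are reused below, so they were checked first.
- n = 1.96² × 0.5 × 0.5 / 0.075² = 170.7, rounded up to 171, as stated.
- Design effect = 1 + (5 − 1) × 0.20 = 1.8, as stated.
- 171 × 1.8 = 307.8, rounded up to 308, as stated. 20 hospitals × 16 = 320, as planned.

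**4. How large might a shift be relative to sampling error?** Inputs from the article: 16 women per hospital and 4 feasibility hospitals, so 4 × 16 = 64 before; about 100 after; adherence 50%; design effect 1.8. The figure of 64 assumes that the before group is limited to the four hospitals. The text could also mean all 320, so both are shown.

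The size of the shift is an assumption. If true adherence is 50% in both periods and the reader resolves 10% to 20% of non-adherent items more favourably in the later reading:
- 0.50 + 0.10 × 0.50 = 0.55
- 0.50 + 0.20 × 0.50 = 0.60

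This is a false gain of 5 to 10 points.

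Standard error of the difference = √[1.8 × 0.25 × (1/n_before + 1/n_after)]:
- 64 and 100: √(0.45 × 0.025625) = 0.107. The shift is 0.05/0.107 = 0.5 to 0.10/0.107 = 0.9 standard errors.
- 320 and 100: √(0.45 × 0.013125) = 0.077. The shift is 0.05/0.077 = 0.6 to 0.10/0.077 = 1.3 standard errors.

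**5. Chance of a nominally significant result with no true effect** (two-sided 5% pooled two-proportion z-test, sample sizes divided by 1.8):

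| Assumed shift | 64 before, 100 after | 320 before, 100 after |
|---|---|---|
| none | 5% | 5% |
| 5 points | 7.5% | 9.9% |
| 10 points | 15.5% | 25.3% |

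The shift does not shrink as the sample grows, so a larger before group makes a false result more likely.

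**The case against.** The strongest reply is that this is a condensed article. Masking, reading order and sampling of the double-read subset are details that a full protocol may hold, and silence does not mean they are absent. That stands against several readings that a reader might infer:
- **That scoring is open.** The article does not say so; it only describes no masking.
- **That the double-read subset misses one period, or that its reader knows the period.** Neither is stated. Since the same method is applied afterwards, a subset may well be read twice in both periods, and that could reveal some drift.
- **That the readers developed the strategy.** The Design section does not name the developers.
- **That the whole effect is confounded.** Part of adherence comes from medical records. The indicators are to be turned into measurable elements after an expert-panel procedure, which limits discretion. How much judgement they will need is not yet known.

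The stakes are also limited. The feasibility study seeks only an indication of effect, and the Discussion reserves effectiveness for a randomised study. The sentence naming the readers belongs to the cross-sectional actual care study, where no change over time is estimated; the problem arises only when the feasibility study adopts that measurement as its comparator.

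The sequence itself survives this reply. It is fixed by the article and does not depend on what it omits. Even if readers were masked at each reading, using the early baseline scores would still tie reading time to period. Double reading of a subset can measure agreement, but it does not put the two periods on one scale unless both are read together, and a project leader may share the researcher's expectation.

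**Conclusion.** The concern holds in a limited form. The design forces baseline video to be scored first, takes that measurement as the comparator for recordings scored later, and has no concurrent control. As described, any reader drift or expectation in the video-scored part of adherence cannot be told apart from a real change, and the planned multilevel analysis does not help. The bias would carry into the cost comparison.

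Its size cannot be derived from the article. For an assumed shift of 5 to 10 points it is 0.5 to 0.9 standard errors with 64 before, 100 after, 50% adherence and a design effect of 1.8. The design effect is borrowed from the actual care study, and the two samples are treated as independent. The result is a reason to strengthen the measurement, not evidence that a shift will occur or that the before-after result would be without value.

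**What to change.** In evaluation a) of the Intervention section:
- State which women form the before group. If it is limited to the four feasibility hospitals, that is about 64.
- Keep their recordings until the after-measurement is complete. This has to be decided before any baseline video is discarded.
- Pool them with the about 100 after recordings, strip date and period labels, and have the existing researcher score the pool in random order.
- Use these scores for the before-after comparison and the cost comparison. Keep the first baseline scores for Objective 1 and for developing the strategy.
- Draw the project leader's random subset from the same pool, stratified by period, and report agreement in each period.
- Abstract record-based items with dates hidden where possible.

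Cost: about 64 recordings are scored a second time (more if the before group is wider), with no change to sample size or recruitment. Images are kept longer, which must be checked against the consent described under Study population, Patients.

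Masking will be imperfect: the researcher may recognise recordings already seen, and elements of the strategy may be visible on screen. Random mixing still breaks the link between period and reading time, which removes drift; expectation is reduced only as far as the masking works.

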### Study population

#### Hospitals

In order to obtain a representative view on the actual care in the Netherlands, 20 hospitals of different regions will participate in this trial including 4 academical, 8 non academical teaching and 8 non academical-non teaching hospitals. The study is set in a Dutch Perinatal Research Consortium, in which all the participating clinics collaborate.

#### Patients

All patients 18 years and older with a higher risk for PPH who will deliver in one of the participating hospitals can be included (16 patients per hospital). This will include women with PPH in a previous delivery, multiple pregnancy, polyhydramnion, chorio-amnionitis, uterus myomatosus, grande multiparity, long delivery, clotting disorders or thrombocytopenia (HELLP). Since asking permission during the delivery is difficult and the higher risk of PPH can develop during delivery, all women who visit the antenatal clinic will be asked in advance by research nurses to participate. Informed consent will be asked for filming the third stage of labour and for reviewing these images by a third party; the researcher. The group who declines will be asked permission to study their medical record. In this way, besides the total incidence of PPH in the study period, the incidence of PPH in women who participate and those who do not participate can be recorded

### Objective 2

To detect barriers and facilitators amongst professionals involved in the implementation of the NVOG-guideline on PPH and the MOET-instructions and patients (barriers and facilitators study).

